### 2.10 Statistical analyses

All analyses will follow the intention-to-treat principle, with additional per-protocol sensitivity analyses. Baseline characteristics will be summarized using means for continuous variables and frequencies (%) for categorical variables, without statistical testing between groups.

For the primary outcome (VAS pain), between-group differences will be analyzed using linear mixed-effects models, with participants included as random effects and baseline scores and minimization factors included as fixed covariates. The primary analysis will focus on the change from baseline to week 12, adjusted for baseline values, to provide a more precise estimate of the treatment effect. This approach allows all available baseline and follow-up data to be used, even in the presence of missing outcomes, under the assumption that data are missing at random. If the assumption of normally distributed residuals is violated, generalized linear mixed models will be considered as an alternative.

Secondary continuous outcomes (FFI – foot pain, FFI – disability, FFI – activity limitation, EQ-5D-5L index) will be analyzed using the same approach. The Global Rating of Change (GROC) will be modelled using ordinal logistic regression; a dichotomized responder analysis (effective vs ineffective) will be presented as exploratory. No formal multiplicity adjustments will be applied, but results will be interpreted with caution.

If missing data exceed 10% for the primary outcome, multiple imputation by chained equations will be used as a sensitivity approach, including all variables related to missingness and outcome prediction in the imputation model. Sensitivity analyses will also be performed under non-Missing At Random assumptions (e.g., using delta-adjustment or pattern-mixture models) to assess the robustness of the findings to departures from the Missing At Random assumption.

Concomitant care and rescue medication use will be recorded descriptively throughout the trial and summarized by treatment group. If substantial between-group differences are observed, these variables will be considered in sensitivity analyses.

The plantar pressure will be divided in nine-foot regions [39]. The analyses will be analyzed with Statistical Parametric Mapping (SPM1D, www.spm1d.org). We will assess the normality of the distribution of the peak plantar pressure (spm1d.stats.normality.anova1rm function) and followed by SPM paired t-tests SPM(t) as post hoc analyses will be used to compare the peak plantar pressure across with and without FOs, when the data will be normally distributed. The non-parametric version, SnPM(t) tests, will be use when data will not normally distributed.

All this will be carried out in frequency distribution tables of different categories, using SPSS (IBM SPSS Statistics: V.28, USA) and plantar pressure will be implemented in MATLAB R2024b (The MathWorks Inc., Boston, MA, USA) using open access scripts (www.spm1d.org).

No additional analyses (e.g., subgroup and adjusted analyses) are planned for this study. The two-sided level of p will be set at 0.050.

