### 2.9 Sample size

To calculate pooled variance (σp²) and square of detectable difference (Δ²), we relied on pain data from a 3-month clinical trial with customized foot orthoses [6] and sham FOs [38].

**Pooled standard deviation:** σ_p_ ≈ 2.71 → σ_p_² ≈ 7.34**Detectable difference:** Δ = 1.49 → Δ² ≈ 2.22**Justification of Δ:** δ = 1.49 corresponds to the minimum clinically important difference on the VAS (≈15% of the scale), based on the study by Reina-Bueno, Vázquez-Bautista [38].α = 0.05β = 0.2**Sum of critical values squared:** (Z_1−α/2_ + Z_1−β_)² = (1.96 + 0.84)² ≈ 7.84

Considering the longitudinal design with three repeated measurements per participant (baseline, 6 weeks and 12 weeks), we estimated the effective variance per subject using a linear mixed-effects model with random intercept:

$${var}_{subj}=\;\sigma_{b}^{\text{2}}+\frac{\sigma_{w}^{\text{2}}}{m}\approx \text{1}.\text{4}\text{6}\text{8}+\;\frac{\text{5}.\text{8}\text{7}\text{2}}{\text{3}}\approx \text{3}.\text{4}\text{2}\text{5}$$

Using this variance, the sample size formula for two independent groups:

$$n\approx \frac{\text{2}\times ({\text{Z}}_{\text{1}-\alpha /\text{2}\;}+\;{\text{Z}}_{\text{1}-\beta })²\;\times {var}_{subj}}{\Delta^{\text{2}}}\approx \text{2}\text{5}$$

Therefore, the minimal sample size would be 25 per group. Considering an attrition rate of 20%, the final sample size should be 32 participants per group, resulting in a total sample size of 64 participants to detect significant differences for the primary outcome (VAS pain) at the primary timepoint (12 weeks). A sensitive analysis table showing required sample sizes under the different correlations (ρ = 0.3, 0.5, 0.7) is available in Supplementary Table S3 in S1 File.

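### As described, the primary mixed model most naturally assumes equal residual variance at weeks 6 and 12; if that fails, the week-12 standard error is wrong

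*Protocol article*

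**What the plan says.** In section 2.10 (Statistical analyses), between-group differences in VAS pain are to be "analyzed using linear mixed-effects models, with participants included as random effects and baseline scores and minimization factors included as fixed covariates". The target is a single visit: "The primary analysis will focus on the change from baseline to week 12, adjusted for baseline values". The continuous secondary outcomes (three FFI domains and the EQ-5D-5L index) follow the same approach, and "The two-sided level of p will be set at 0.050".

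Section 2.9 (Sample size) is the only place that names the form of the random effect: "we estimated the effective variance per subject using a linear mixed-effects model with random intercept". It starts from one SD for all visits, "σ_p_ ≈ 2.71 → σ_p_² ≈ 7.34", and splits that variance into a between-subject part of 1.468 and a single within-subject part of 5.872.

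The article gives no SD for an individual visit. It does not say whether the residual variance may differ between weeks 6 and 12, and it mentions neither a baseline-by-visit term nor a degrees-of-freedom method.

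**The concern.** A participant random intercept with one residual variance gives every follow-up visit the same variance. That suits a treatment effect averaged over visits. Here the contrast is at week 12 only, so its standard error should reflect the week-12 residual variance. Under the model as described, it reflects the mean of the week-6 and week-12 variances.

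The two variances could differ in two ways. The raw spread of pain scores may change between visits, for example if participants respond unequally. Or the raw spread may stay constant while the correlation with baseline fades, so that baseline explains less at week 12 than at week 6.

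If week 12 is the more variable visit, the confidence interval is too narrow and the false-positive rate exceeds the stated 5%. If it is the less variable visit, the interval is too wide and power is lost. The same would apply to the FFI domains and the EQ-5D-5L index.

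**Working it through.** **1. The plan's own figure.** Section 2.9 gives a variance per subject of 1.468 + 5.872/3 = 3.425. Then n = 2 × 7.84 × 3.425 / 2.22 = 24.2, so 25 per group. With 20% attrition, 25/0.8 = 31.25, so 32 per group and 64 in total. The figure reproduces. The implied correlation between visits is 1.468/7.34 = 0.20.

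**2. What the model uses for week 12.** Take weeks 6 and 12 as outcomes, baseline as a covariate, a group-by-visit term and complete data. Let v6 and v12 be the residual variances and c their covariance. The week-12 value equals the mean of the two visits plus half their difference. The random-intercept model treats these two pieces as independent, so its variance for week 12 is

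(v6 + v12 + 2c)/4 + (v6 + v12 − 2c)/4 = (v6 + v12)/2,

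while the true variance is v12. With r = residual SD at week 12 / residual SD at week 6,

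model SE / true SE = √[(1 + 1/r²)/2].

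- r = 1.25: √[(1 + 0.64)/2] = 0.906
- r = 1.10: √[(1 + 0.826)/2] = 0.956
- r = 0.80: √[(1 + 1.5625)/2] = 1.132

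Simulated null trials at 32 per arm agree (20,000 each; assumed residual SD 2.4 at week 6, baseline SD 1.5, residual correlation 0.4). The ratios were 0.904, 0.957 and 1.129, with type I error of 7.3%, 6.0% and 2.6%. A fit with its own week-12 variance and slope stayed between about 4.8% and 5.3%, across these settings and the same ones at 25 per arm.

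**3. Patterns on the plan's SD scale.** With raw SD s and baseline correlation ρ, the residual variance is s²(1 − ρ²). The values 0.3, 0.5 and 0.7 appear in section 2.9 as alternatives for a sample-size sensitivity table; assigning them to particular visits is an assumption made here, as is the SD of 2.2. All rows have 25 completers per arm and Satterthwaite degrees of freedom, with 8,000 null trials each (20,000 in the last two).

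| SD wk 6, wk 12 | Correlation with baseline, wk 6 then wk 12 | Correlation wk 6–12 | SE ratio by formula | Type I error |
|---|---|---|---|---|
| equal | equal | equal | 1.00 | 4.7% |
| 2.71, 2.71 | 0.7, 0.5 | 0.7 | √(0.63/0.75) = 0.92 | 7.1% |
| 2.71, 2.71 | 0.5, 0.3 | 0.5 | √(0.83/0.91) = 0.96 | 5.8% |
| 2.71, 2.71 | 0.7, 0.3 | 0.5 | √(0.71/0.91) = 0.88 | 8.4% (7.9% in a second run) |
| 2.2, 2.71 | 0.5, 0.5 | 0.5 | √(4.57/5.51) = 0.91 | 7.0% |
| 2.71, 2.2 | 0.5, 0.5 | 0.5 | √(4.57/3.63) = 1.12 | 3.0% |
| 2.71, 2.71 | 0.2, 0.1 | 0.2 | √(0.975/0.99) = 0.99 | 5.0% |
| 2.71, 2.71 | 0.2, 0 | 0.2 | √(0.98/1) = 0.99 | 5.2% |

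In the first six rows, a fit with its own week-12 variance and slope gave 4.8% to 5.0%.

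**4. The baseline slope on its own.** Fitting one slope when the true slopes are b6 and b12 adds ((b6 − b12)/2)² × baseline variance to both visits' residuals. The addition is equal, so the average stays right for week 12. With equal residual variances and 32 per arm, slopes of 0.7 and 0.3 gave an SE ratio of 1.002 and type I error of 4.7%; slopes of 0.9 and 0.1 gave 1.009 and 4.6%. The cost is precision: at 25 per arm in that extreme case the true SE was 0.707 instead of 0.690, about 2.5% larger.

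**The case against.** The strongest reply is that section 2.10 does not say what is held against it. It names participants as random effects and stops there; the term random intercept belongs to the sample-size section. A participant random effect can be combined with visit-specific residual variances and a baseline-by-visit term, and the article excludes neither. Covariance structure and degrees of freedom are often settled in a statistical analysis plan, which is not shown. This stands in part: one cannot say that the plan forces equal variances. But the article does more than stay silent. It commits to a random-effects structure, and section 2.9 describes one with a single within-subject variance. That is a choice that can be judged against a week-12 contrast.

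A second reply is that the size is hypothetical. This stands. No visit-specific SD and no lag-specific correlation is given, the error can go either way, and at the plan's implied correlation of 0.20 a fading baseline correlation hardly matters.

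A reader might also infer that the standard error is wrong unless both equal variances and a common baseline slope hold. That goes too far: unequal slopes alone leave it valid in complete data. They matter for validity only where they come with unequal residual variances, as when the raw SD is constant and the baseline correlation fades. Dropout that depends on baseline could change this, but that is a different argument and was not examined here.

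**Conclusion.** The point holds as a conditional one. On its natural reading, the primary model assumes equal residual variance at weeks 6 and 12, and the week-12 standard error is correct only if that is so. In the patterns tried, the standard error was between about 12% too small and 13% too large, and type I error ran from about 3% to 8%. With equal variances, or at the implied correlation of 0.20 with equal SDs, it was close to 5%.

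These figures rest on complete data, weeks 6 and 12 as the outcomes, a group-by-visit term, and assumed SDs and correlations. They show what could happen and do not predict this trial. The documents do not support saying that the test is invalid, that it is anti-conservative rather than conservative, or that equal variances are imposed beyond doubt. A change is worthwhile because it affects the primary test and four secondary measures, the assumption is unsupported by any visit-level figure, and a method that does not need it costs almost nothing.

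**What to change.** In section 2.10, specify the model for weeks 6 and 12 with an unstructured (visit-specific) covariance in place of the participant random intercept. Include treatment-by-visit and baseline-by-visit terms, keep the minimization factors as covariates, fit by REML, and use Kenward-Roger or Satterthwaite degrees of freedom. State that the treatment effect is read at week 12. Use the same structure for the three FFI domains and the EQ-5D-5L index.

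The cost is a sentence or two of text. The unstructured covariance over two visits has three parameters against two for the random intercept, and there is one additional baseline slope. With 50 completers planned and 64 randomized, that is negligible. No extra data or participants are needed, and the sample size is unaffected by this change.

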### 2.5 Data collection

Once the FOs are manufactured, participants will return to UQTR to collect them. During this visit, they will complete the initial questionnaires, and plantar pressure measurements will be taken with and without FOs. The plantar pressure will be collected with a Pedar-X in-shoe pressure measurement system (Novel Corporation, Munich, Germany), sampling at 100 Hz. The insoles of this system will be inserted between the foot and either the insole of the shoe or the FOs. Once they are equipped with the plantar pressure system, the participants will be allowed five minutes of acclimatization. Then, they will walk 10 times at a self-selected speed on a 10-meter walkway. The second and third assessments will be completed by phone or visioconference by a member of the research team, blinded to the group allocation of the participants. We will use MATLAB R2024b (The MathWorks Inc., Boston, MA, USA) for randomization and Qualtrics for the questionnaires.

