#### 2.8.3 Other variables.

Gender: Male, female or other.Age: in years (from the date of birth).Weight: in kg (measured in clinic).Height: in meters (measured in clinic).Body Mass Index (BMI): will be calculated with the formula weight (Kg) divided by height squared (meters^2^).Foot Posture Index (FPI): The six clinical criteria used in FPI are: 1. Palpation of the talus head (medial and lateral deviation of the talus head in relation to the navicular bone); 2. Curvature of the supra and lateral inframaleolar region; 3. Position of the calcaneus in the frontal plane; 4. Prominence of the talonavicular region; 5. Congruence of the internal longitudinal arche; and 6. Abduction/adduction of the forefoot with respect to the rearfoot. Each criterion is rated between −2 and +2 and the sum of all gives a total score indicating the foot posture (Normal = 0 to +5; pronated = +6 to +9; highly pronated = +10 to +12; supinated = −1 to −4 and highly supinated = −5 to −12).Effects of the FOs on plantar pressure: peak plantar pressure during a stance phase (kPa) under the metatarsal heads, measured with a Pedar-X in-shoe pressure measurement system (Novel Corporation, Munich, Germany). This system is repeatable and can be used as a valuable tool in the assessment of in-shoe plantar pressure distribution [35–37].

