### 3.1 Limitations

The sham FOs that we will use are a credible intervention (i.e., participants rated them as credible) and have the same effects on plantar pressure under the midfoot and forefoot than shoes [27]. However, biomechanical analyses of these orthoses showed that they reduce plantar pressure under the heel compared to shoes [27]. By evaluating the effects of the experimental conditions (Customized and sham FOs) during the baseline sessions, we will ensure that customized FOs reduce plantar pressure under the lesser metatarsal heads and that sham FOs provide negligible effects.

Although participants will be asked to limit the use of anti-inflammatory drugs and medications, it will not be possible to prevent them from taking these. This intake may impact the pain measured in the primary outcome.

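### The planned paired pressure tests can support offloading by the customised orthoses, but they cannot show that the sham effect is negligible, and the two devices are never compared

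*Protocol article*

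**What the plan says.** - Section 2.5 (Data collection): at the visit when the devices are collected, "plantar pressure measurements will be taken with and without FOs", so each participant contributes both conditions.
- Section 2.8.3 (Other variables) defines the measure as "peak plantar pressure during a stance phase (kPa) under the metatarsal heads".
- Section 2.10 (Statistical analyses): "The plantar pressure will be divided in nine-foot regions" and "The analyses will be analyzed with Statistical Parametric Mapping (SPM1D, www.spm1d.org"). Normality is checked with the "spm1d.stats.normality.anova1rm function", and then "SPM paired t-tests SPM(t) as post hoc analyses will be used to compare the peak plantar pressure across with and without FOs", with a non-parametric version if normality fails. The section closes with "No additional analyses (e.g., subgroup and adjusted analyses) are planned for this study" and a two-sided level of 0.05.
- Section 3.1 (Limitations) states what these data are for: "we will ensure that customized FOs reduce plantar pressure under the lesser metatarsal heads and that sham FOs provide negligible effects".

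**The concern.** The claim in section 3.1 has two halves of different kinds. That the customised device lowers pressure is a claim of a difference, which a difference test can support. That the sham does almost nothing is a claim of near-absence of effect. A difference test can only fail to contradict it, and how much such a failure means depends on precision and on what counts as negligible. The article gives no margin.

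The text also leaves open whether the paired tests are run separately by arm. If the arms were pooled, neither half would be tested. If they are run by arm, readers will be inclined to contrast a significant result in one arm with a non-significant one in the other, which is not a test that the devices differ.

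What is at stake is interpretation. Section 1 builds the case for the device on forefoot offloading, and sections 2.3.2 and 3.1 rest the control on a sham that leaves the forefoot unchanged. The baseline pressure data are the only check of this described within the trial itself.

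**Working it through.** **Inputs.** Group size comes from section 2.9 and the two-sided 0.05 level from section 2.10. The documents give neither an SD for the pressure change in kPa nor a margin. Effects are therefore in SDs of the with-minus-without difference, and the ranges used are assumptions.

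**1. The plan's own figure.** Section 2.9 gives n = 2 × 7.84 × 3.425 / 2.22 = 24.19, rounded up to 25 per group. Then 25 / 0.80 = 31.25, rounded up to 32 per group and 64 in total. This reproduces, but it is sized for VAS pain. No figure is given for pressure.

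**2. Precision within the sham arm.** The 95% half-width is t(0.975; n−1)/√n. For n = 32 it is 2.04/√32 = 0.36 SD. For n = 25 (the size after the assumed 20% loss) it is 0.41 SD. Pressure is measured at device collection, so 32 is the more natural figure.

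**3. How often a real sham effect would be missed.** The power of a paired t-test with n = 32 comes from the non-central t distribution (31 df, non-centrality d√32). The last column is power × (1 − power): the chance that the customised arm is significant and the sham arm is not when both devices have the same true effect d (equal SDs, independent arms).

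| True change d (SD) | Power | Non-significant | Customised significant, sham not |
|---|---|---|---|
| 0.2 | 0.195 | 0.805 | 0.195 × 0.805 = 0.16 |
| 0.3 | 0.376 | 0.624 | 0.376 × 0.624 = 0.23 |
| 0.4 | 0.592 | 0.408 | 0.592 × 0.408 = 0.24 |
| 0.5 | 0.782 | 0.218 | 0.782 × 0.218 = 0.17 |

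Power reaches 80% at d = 0.51.

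**4. What a proper test of negligible could deliver.** Two one-sided tests at 0.05 with n = 32 and a true sham effect of zero (100,000 simulated trials) have power of 7%, 43%, 74% and 91% for margins of 0.3, 0.4, 0.5 and 0.6 SD.

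**5. A between-arm comparison.** A two-sample comparison of the changes with 32 per arm, unadjusted, has 80% power at 0.71 SD.

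**6. Variable and method side by side.** Section 2.8.3 reads most naturally as one maximum per stance phase under the metatarsal heads. Section 2.10 uses a package for one-dimensional curves, divides the foot into nine regions, checks normality with a repeated-measures ANOVA routine, and calls the paired tests post hoc although no ANOVA is stated. Two analysts could not be sure of running the same analysis.

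**The case against.** The strongest reply is that section 3.1 makes two statements, each about one device, and neither is a comparison between arms. A paired with-versus-without contrast is the direct test of whether the customised device lowers pressure. This stands. A reader might infer that the plan can support neither half of the claim, and that goes too far: the offloading half needs only a statement that the test is run by arm.

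Three other strong readings are tempting and not supported.

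- *That a curve-based method makes the inference invalid.* The text may intend a peak-pressure curve over stance, and the choice of SPM1D points that way. If the value is a scalar, SPM(t) at a single point is an ordinary paired t-test. This is an ambiguity to resolve.
- *That nine regions carry a 37% false-positive risk.* The figure 1 − 0.95⁹ = 0.37 needs independent regions, no true effect anywhere, and inference on all nine. Regions of one foot are plausibly correlated, sections 2.3.2 and 3.1 already expect a heel effect from the sham, and section 2.8.3 confines the variable to the metatarsal heads.
- *That the authors will declare the sham negligible from a non-significant result.* No section states that rule. The point is that the planned test gives nothing better on which to base the claim.

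It can also be said that a margin and a by-arm statement belong in an analysis plan that is not shown. That has some force. However, the article itself names the test, routine and level, says no additional analyses are planned, and makes the claim. The mismatch is between its own sections.

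Finally, averaging over ten walks could make the SD of the differences small, so that 0.36 SD is trivial in kPa. That is possible and cannot be checked from the document. The case for the sham also rests on earlier validation cited in sections 2.3.2 and 3.1, so it does not depend on these data alone.

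**Conclusion.** The point holds in limited form. As written, the plan can support the statement that customised orthoses reduce pressure under the lesser metatarsal heads, provided the paired test is run in that arm. It cannot support the statement that the sham effect is negligible, because a difference test without a margin leaves changes of up to about 0.36 SD either side of the estimate open. It also provides no test of whether the devices differ, and separate significance results by arm would mislead in about 16% to 24% of trials if the true effects were equal and between 0.2 and 0.5 SD.

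These sizes assume 32 measured per arm and approximately normal differences. Their meaning in kPa is unknown. Plantar pressure is listed among other variables, so the pain, FFI, GROC and EQ-5D-5L analyses are unaffected. This is a cheap improvement to the supporting evidence and does not bear on the validity of the trial.

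**What to change.** 1. Run the paired contrast separately by arm, on peak pressure under the lesser metatarsal heads.
2. Report the within-sham mean change with its confidence interval against a margin fixed in advance in kPa. If no margin can be justified, replace the wording in section 3.1 with a statement that the sham effect will be estimated.
3. Add a between-arm comparison of the with-device value, adjusted for the without-device value, with a 95% confidence interval.
4. State whether the variable is a scalar or a stance-phase curve. Keep SPM1D only for curves, and drop the ANOVA normality routine and the post hoc label unless an ANOVA is planned.
5. Treat the remaining regions as descriptive.

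The cost is analysis wording, slightly more analysis work, and probably a softer claim about the sham. No new data are needed.
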